Clinical guidelines for the management of low back pain consistently recommend staying active [2] with evidence suggesting that maintaining an active lifestyle leads to reduced pain and improved functional outcome [22]. It is not known whether this positive association can be translated into the post-surgical population, or more specifically, whether people who participate in more physical activity have better outcomes following surgery. In other post-surgical populations, evidence suggests that early and increased walking improves functional outcome and reduces the rate of post-operative complications [23]. It is therefore likely that increased walking immediately following lumbar spinal surgery leads to similarly improved outcomes.

Accelerometers are becoming an increasing popular method of quantifying physical activity, and have been shown to provide an accurate measure of step count, time spent walking and distance walked. [24–26] Two recent studies have used accelerometry to describe the improvement in physical activity following lumbar spinal surgery. Mobbs et al. [27] reported a significant improvement in step count and distance walked three months after lumbar spinal surgery, and Schulte et al. [28] reported a significant improvement in step count three months after surgery for lumbar stenosis. There are however, no known studies describing walking immediately following spinal surgery, or how the amount of walking in this period impacts longer-term functional recovery.

We know that gait assessment, and advice regarding walking and return to physical activity already forms a key component of physiotherapy intervention immediately following lumbar surgery. Establishing how much walking patients currently do, and how walking in the period immediately following surgery impacts longer term functional outcome will enable physiotherapists to individualise patient management to achieve optimal outcomes. It will also help to identify patients who are unable to achieve the minimum amount of walking associated with improved outcomes, and who may therefore require more intensive rehabilitation programmes.

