### Study procedure

#### Recruitment and sample size

The recommended sample size for logistic regression analysis is a minimum of 5 outcome events per predictor variable (EPV) [29]. The maximum number of variables to be analysed in this study is 15 giving a minimum sample size of 150. Based on expected admissions to the treating institution over the recruitment period, it is expected that this will provide an estimated recruitment pool of 300 eligible participants and sample size of approximately 250 participants. This proposed sample size allows for variation in EVP, missing data and participants lost to follow-up.

Patients undergoing lumbar spinal surgery will be identified from the surgical lists. All eligible patients will be provided with an information pack containing a participant information statement, consent form, withdrawal of consent form and baseline outcome measures. The research physiotherapist will contact potential participants during the week prior to surgery to confirm eligibility and respond to any questions. Written consent will be obtained from all participants. Consent forms and baseline outcome measures will be collected from participants following admission to hospital. Demographic data and information about the surgical procedure will be collected from the participant and patient records during admission.

Following surgery, all participants will be fitted with an activPAL3 accelerometer (PAL technologies) to be worn for the first seven post-operative days, commencing the morning after the day of surgery. As per the manufacturer instructions, the accelerometer will be fixed to the upper thigh using a waterproof transparent Tegaderm dressing. This can then remain in place for the seven-day monitoring period, with a daily review to check for discomfort or irritation. This method of fixing the accelerometer to the thigh eliminates the need for participants to remove and apply the monitoring device for showering and sleeping, it does not require participants to wear a waist band or belt that would sit across the site of the lumbar surgery.

Where participants are discharged during the seven-day monitoring period they will be provided with information regarding the use and removal of the accelerometer, and a reply paid envelope to return the accelerometer to the researcher.

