#### Independent (predictor) variable

The predictor variable to be used in data analysis will be the total time spent walking (recorded as total time performing stepping activity) over the first seven post-operative days. This data will be recorded using an activPAL3 accelerometer and downloaded using software provided by PALtechnologies. The activPAL3 accelerometers provide a user-friendly measure of posture and walking with robust evidence for validity and sufficient reproducibility for this study [24–26]. As the activPAL3 accelerometer is worn on the thigh, the accuracy of the monitor is not reliant on arm swing and is not expected to vary if participants are using a gait aid.

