#### Relationship between time spent walking and outcome

Multivariable logistic regression analysis will be used to investigate the relationship between the time spent walking in the first week after surgery and outcome at six months using SPSS software. The dependent variable in the logistic regression model will be the change in score on the ODQ, SF-36 (PCS), NRPS (back) and NRPS (leg) between baseline and six months. The change in scores on the ODQ, SF-36 (PCS) and NRPS will be dichotomised based on the threshold required to demonstrate a substantial clinical benefit.

Thresholds required to meet the minimum clinically important difference (MCID) have been identified for the ODQ, the SF-36 (PCS) and the NPRS [41] (Table 2). In addition, thresholds required to obtain a substantial clinical benefit (SCB), where patients report a major improvement in symptoms, have been defined for the ODQ, SF-36 (PCS) and NRPS in the lumbar fusion population [42] (Table 2). For the purpose of this study it has been assumed that SCB following lumbar fusion surgery provides a fair estimate of substantial clinical benefit following lumbar surgery in general. These thresholds allow the change in scores to be categorised as minimal improvement (below MCID threshold), moderate improvement (above MCID threshold, below SCB threshold) and substantial improvement (SCB threshold or greater).

**Table 2 Tab2:** MCID and SCB thresholds

Outcome measurement tool	MCID (points change)	SCB (points change)
ODQ	10	18.8
SF-36 (PCS)	4.9	6.2
NPRS (back)	2	2.5
NRPS (leg)	2	2.5

As all participants in this study are undergoing surgery with the aim of improving pain and physical function, it expected that the majority of participants in this study will report an improvement in scores above the MCID threshold. Therefore the SCB threshold will be used to analyse the impact of walking time on outcome (minimal/moderate improvement compared to substantial improvement). For each of the four dependent variables a multivariable logistic regression model will be generated comparing participant outcome relative to the SCB threshold.

With the exception of pre-operative function and surgical procedure, all confounding variables will be dichotomised (Table 3).

**Table 3 Tab3:** List of independent variables and classification for statistical analysis

	Classification				
1. Post-operative activity	Time spent walking (minutes)				
2. Age	1. < 65 years	2. ≥ 65 years			
3. Gender	1. Male	2. Female			

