4. Current smoking status	1. Non-smoker	2. Smoker			
5. Obesity	1. BMI < 30	2. BMI ≥ 30			
6. Diabetes	1. Not diabetic	2. Diabetic			
7. Depression	1. PHQ-9 < 10	2. PHQ-9 ≥ 10			
8. Anxiety	1. GAD-7 < 10	2. GAD-7 ≥ 10			
9. Duration of pain/symptoms	1. < median (months)	2. ≥ median (months)			
10. Neurological deficit	1. No deficit	2. Neurological deficit			
11. Pre-operative activity	1. IPAQ-SF - Mod/high	2. IPAQ-SF - low			
12. Pre-operative mobility	1. ODQ (section 4) < 3	2. ODQ (section 4) ≥ 3			
13. Surgical procedure	1. Decompression	2. Disc surgery	3. Fusion		
14. Multi-level surgery	1. Single level surgery	2. Multi-level surgery			
15. Preoperative function (ODQ%)	1. 0–20	2. 21–40	3. 41–60	4. 61–80	5. 81–100

Bivariate analyses will be carried out to assess the association between each confounding variable and each outcome measure. The variables that have an independent association with outcome will be included in the final regression model. Analysis of correlation between the independent variables will be carried out to assess for multicollinearity. Where variables are highly correlated, either the more relevant variable or the variable with the more complete data set will be retained in the final regression model [43].

Missing independent variable data will be managed based on the quantity of missing data per participant and per variable. In the case of missing or incomplete accelerometry data, participants will be removed from analysis where three or more days of recordings are missing. In the case of one to two days of missing data, the time spent walking each day will be estimated based on the mean daily walking time of the total sample population. Comparisons will be made between the characteristics of participants with and without missing data to ensure minimisation of bias [43]. The underlying assumptions of the model will be assessed using the SPSS software “goodness of fit” testing.

Bivariate analysis will be used to examine the association between post-operative walking time, and both patient satisfaction and post-operative complications as reported at six months.

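### The stated goodness-of-fit check is a weak test of whether walking minutes act linearly on the log-odds, and a single slope cannot show a minimum useful amount of walking

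*Protocol article*

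**What the plan says.** In the protocol article, under Relationship between time spent walking and outcome, the plan is: "For each of the four dependent variables a multivariable logistic regression model will be generated comparing participant outcome relative to the SCB threshold". The exposure is the "total time spent walking (recorded as total time performing stepping activity) over the first seven post-operative days" (Independent (predictor) variable). Table 3 lists it in minutes, without categories, transformation or any further term. The 14 confounders in the same table are all put into classes: most into two, surgical procedure into three and pre-operative function into five.

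Two model checks are stated. One is collinearity: "Analysis of correlation between the independent variables will be carried out to assess for multicollinearity". The other covers everything else: "The underlying assumptions of the model will be assessed using the SPSS software" goodness-of-fit testing. The particular test is not named.

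The Background expects the work to help "identify patients who are unable to achieve the minimum amount of walking associated with improved outcomes". None of the three research questions under Aims asks for such a minimum.

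**The concern.** Entering one untransformed continuous term in a logistic model assumes that each extra minute changes the log-odds of substantial benefit by the same amount, however much the patient already walks. With the confounders entered as classes, this assumption applies to one term only, and that term answers the primary question.

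The plan assigns the checking of assumptions to an overall fit test. Such a test compares observed and predicted events across the whole model. Hosmer-Lemeshow, for example, groups patients by total fitted risk. Once several confounders contribute to that risk, patients with very different walking times share a group, and a bend in the walking effect is averaged away.

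At stake is how the result is described. If benefit levels off, one odds ratio understates the gain among those who walk little and overstates it among those who walk a lot. A non-significant fit test could then be reported as support for the straight line when it had little chance of showing otherwise.

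**Working it through.** **1. The plan's own sample-size figure.** Recruitment and sample size uses 5 events per variable and 15 variables: 5 × 15 = 75 events. The stated minimum of 150 participants then implies an event proportion of 75 / 150 = 50%, which the article does not state. The figure reproduces and is not in dispute. It is used in the fix to price the extra term.

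**2. What each stated check can see.**

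| Stated check | What it examines | Shape of the walking effect? |
|---|---|---|
| Correlation among independent variables | Collinearity | No |
| SPSS goodness of fit | Overall agreement of observed and predicted events | Only indirectly |

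**3. Main simulation.** From the documents: logistic model, one linear walking term, categorical confounders, up to about 250 participants. Assumed: Hosmer-Lemeshow with 10 groups; significance level 0.05; gamma walking time (shape 2.5, right-skewed); benefit rising to the median and then flat, logit = B × (min(x, median) − 1.5) plus confounder effects, with B from 0.8 to 1.2; binary confounders; n = 200 to 250. The linear model is fitted and two tests are compared on the same data: Hosmer-Lemeshow, and the 1-df likelihood-ratio test of the extra term in a 3-knot restricted cubic spline.

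| Confounders in model | Hosmer-Lemeshow rejects |
|---|---|
| 0 | 27-57% |
| 1 | 12-38% |
| 3 | 6-14% |
| 5 or 8 | 2-10% |

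Over the same settings the spline test rejects 48-92%, and it is the stronger test in every setting.

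**4. Second simulation, different assumptions.** Log-normal walking time (median 300 minutes, log-SD 0.6), event rate about 50%, threshold and plateau shapes with odds ratios of 3 to 5, n = 250, 600 replicates per setting. The direct test here is a 4-knot spline (2 df).

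| Confounders | Hosmer-Lemeshow rejects |
|---|---|
| 0 | 40-80% |
| 1 | 24-52% |
| 2 | 12-26% |
| 3 | 8-19% |
| 5 | 4-9% |
| 13 | 4-6% |

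The spline test rejects 46-93% across these runs. Box-Tidwell rejects 46-79% with five confounders and 41-76% with 13. With less skewed walking (log-SD 0.35) and about 65% events, Hosmer-Lemeshow rejects 10-23% with two confounders, 6-9% with five and 5-8% with eight, against 36-88% for the spline.

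**5. Are the direct tests merely over-rejecting?** When the true effect was linear (n = 250, one or more confounders), the 4-knot spline test rejected 4.5-7.7% and Hosmer-Lemeshow 4.0-5.5%. With 600 replicates the standard error at 5% is √(0.05 × 0.95 / 600) = 0.9 points. Any excess is a few points, far too small to explain the gap.

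**6. A minimum amount from a slope.** A single log-odds slope is the same at every walking time. It has no point at which benefit starts or stops, so any minimum read from it would come from a cut-off chosen on the probability scale and not from the fitted shape.

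**The case against.** **Little power is not a general property of the check.** This stands. With no or few confounders retained, Hosmer-Lemeshow detects a plateau in a fair share of studies. The plan retains only confounders associated with outcome, so their number is unknown. A reader might infer that the check has almost no power whatever the final model. The simulations support that only from about five confounders upward.

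**The test is not named.** This also stands: Hosmer-Lemeshow is an assumption. The argument about overall fit does not depend on that choice, but the percentages do.

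**It is not the only check.** Correct. Collinearity is also examined, although it does not bear on linearity.

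**The minimum amount is background.** A reader might infer that the study promises a threshold its model cannot deliver. The research questions promise none, and the Discussion speaks of limited walking time, which a steadily rising slope can serve. The mismatch is confined to the expected use named in the Background.

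**The primary question survives a bend.** Largely true. A linear term still picks up a rising-then-flat effect, and its odds ratio remains readable as an average trend. A reader might infer that the linear term should be replaced to gain power. That is not claimed here, because the change proposed keeps the same primary test. Nothing in the article points to a plateau; the non-linear shapes are assumptions.

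**A condensed article leaves spline details to a fuller plan.** Fair as to knots and plots, whose absence is not the point. The article does more than stay silent: it assigns the assumptions to a particular kind of test.

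**Conclusion.** The point holds in a limited form. The stated check is poorly matched to the assumption that matters most for the primary exposure. It has little power once several confounders are in the model (2-10% with five or eight) and partial power with none or one (12-57%), against about 48-92% for a direct 1-df test on the same data. The ranking is stable across two sets of assumptions; the exact percentages are not.

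The figures rest on the assumed walking-time distributions, the assumed plateau or threshold shapes and the assumption of Hosmer-Lemeshow. The conclusion is about interpretation: a non-significant fit test in a model with several confounders should not be offered as evidence of linearity, and the slope alone cannot supply a minimum amount of walking. It does not show that the primary test is invalid or that the true effect is non-linear. This is an inexpensive improvement that should be made before analysis.

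**What to change.** Keep the 1-df linear walking term as the primary test for each outcome. Reword the goodness-of-fit sentence so that it covers overall fit only, and name the test. Add a pre-specified linearity check: refit each final model with a 3-knot restricted cubic spline for walking minutes (knots at the 10th, 50th and 90th centiles), report the 1-df non-linearity test, and plot the predicted probability of substantial clinical benefit against minutes.

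State in advance what follows. If non-linearity is found, report the curve beside the linear odds ratio and describe that odds ratio as an average trend. Base any statement about a minimum amount of walking on the curve.

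The cost is one extra model per outcome and one extra parameter in that model. By the plan's own rule, 5 × 16 = 80 events, and 80 / 0.50 = 160 participants at the implied event proportion, against about 250 planned. No new data are needed, and no gain in power for the primary test is claimed.

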## Method

### Aims

This research will investigate the relationship between the time spent walking in the week following lumbar surgery, and recovery of physical function. The primary aim is to establish whether the amount of walking patients do in the week following lumbar spinal surgery predicts improvement in function at six months. The data collected will also be used to generate an activity profile to describe the overall patterns of activity in the first post-operative week, and to identify factors that may influence the amount of activity patients undertake.

The research questions are:Does the amount of time spent walking during the week after lumbar spinal surgery predict improvement in function at six months?What proportion of time do patients spend performing active tasks (standing and walking) compared to sedentary behaviour (sitting and lying) in the week following lumbar spinal surgery?Is the amount of time spent walking in the first post-operative week influenced by restricted pre or post operative physical function, post-operative pain or complications, or the need for supervision while walking?

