### Design

This study will be a prospective cohort study design. Ethics approval from the St Vincent’s Hospital Melbourne Human Research Ethics Committee’s has been obtained (Reference: LRR 098/15).

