#### Independent (confounding) variables

Data will be collected for variables where there is either evidence to suggest they influence outcome following lumbar spinal surgery, or there is or strong theoretical rational for their inclusion. This will include age, gender, current smoking status [14, 15], obesity [14, 18], diabetes [14, 16, 17], depression [19, 20], duration of pain/symptoms [35], neurological deficit [14], anxiety, pre-operative activity, pre-operative mobility, surgical procedure, multi-level surgery, and pre-operative function.

Depression will be assessed using the Patient Health Questionnaire Depression Scale (PHQ-9), using a cut off score of ≥10 [36]. The PHQ-9 is a short, valid and reliable measure of depression, and has been recommended for use within the chronic back pain population [37]. Anxiety will be scored using the Generalised Anxiety Disorder 7-item Scale (GAD-7), using a cut off score of ≥10 [38]. The GAD-7 is a brief, seven question scale used to screen for, and assess the severity of anxiety. It has been validated in the general population [38]. Neurological deficit will be assessed by asking the participant if he/she is aware of any changes to the sensation or strength in their affected lower limb. This level of information is deemed appropriate for this study, as any sensory or motor deficit that the participant is unaware of is unlikely to have an impact on functional ability. Pre-operative activity will be assessed using the International Physical Activity Questionnaire Short Form (IPAQ-SF) [39, 40]. The IPAQ-SF is a brief, reliable seven item questionnaire that requires participants to report on physical activity undertaken over the previous seven day period [39, 40]. Physical activity is categorised into low, moderate and high activity levels. As it is expected that the majority of participants will report either low or moderate activity levels, the two categories of low and moderate/high activity levels will be used for data analysis. Baseline ODQ score will be used as a measure of pre-operative function. Pre-operative mobility will be categorised based on the response to Section 4 (Walking) on the ODQ. Participants will be categorised as having limited mobility if they score 3 or more - unable to walk more than 500 m, require a walking aid, or are confined to bed.

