#### Factors associated with time spent walking immediately following surgery

Additional data will be collected on a daily basis regarding post-operative back, leg and wound pain intensity (NRPS), the need for supervision while walking, and surgical/medical complications. Reported complications will include events where the participant requires medical intervention in addition to routine post-operative care, and events that limit activity (for example, symptomatic hypotension, analgesia-induced nausea). This information will be sourced from the patient, ward staff, and patient notes. In cases where participants are discharged from the inpatient facility prior to completing the monitoring period they will be asked to record this information daily, which will then be returned to the researchers with the accelerometer following the completion of the monitoring period.

At six months, participants will be asked to report on overall satisfaction with the results of the surgery, scored on a five point likert scale. They will also be asked to describe any post-operative complications experienced after the seven day monitoring period. This will include any event directly related to the surgical procedure requiring medical intervention in addition to routine follow-up care.

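### Walking time is related to six-month satisfaction and complications by unadjusted analysis only, so these two additional associations are open to confounding

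*Protocol article*

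**What the plan says.** The Design section states: "This study will be a prospective cohort study design". How much a patient walks in the first week is observed, not assigned.

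Under Independent (confounding) variables, the protocol article explains its choice of covariates: "Data will be collected for variables where there is either evidence to suggest they influence outcome following lumbar spinal surgery", or where there is a strong theoretical reason. Table 3 lists 14 of them (items 2 to 15) beside walking time.

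Two kinds of analysis follow in the section Relationship between time spent walking and outcome.

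- **Function and pain** (ODQ, SF-36 PCS, back pain, leg pain): "For each of the four dependent variables a multivariable logistic regression model will be generated comparing participant outcome relative to the SCB threshold". Covariates enter after a bivariate screen: "The variables that have an independent association with outcome will be included in the final regression model".
- **Satisfaction and complications at six months**: bivariate analysis is to "examine the association between post-operative walking time, and both patient satisfaction and post-operative complications as reported at six months". No covariate is named, and no other section adds an adjusted analysis.

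Satisfaction is an ordered outcome: "participants will be asked to report on overall satisfaction with the results of the surgery, scored on a five point likert scale". Complications are those that the patient describes at six months as having occurred after the seven-day monitoring period.

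**The concern.** The plan treats some of the same variables as possible causes of both exposure and outcome. The third research question in Aims asks: "Is the amount of time spent walking in the first post-operative week influenced by restricted pre or post operative physical function". The section Factors associated with post-operative walking time then relates walking time to pre-operative mobility, function and physical activity. All three are also on the confounder list, as variables thought to influence outcome after surgery. If they do both, patients who walk less will tend to have worse six-month results even if walking itself does nothing.

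For function and pain the plan guards against this, at least in part. For satisfaction and complications it does not.

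What is at stake is interpretation. The Background says that early walking reduces complications in other surgical populations and expects a similar benefit here. The Discussion says the findings will inform whether increasing activity should be a focus of rehabilitation. A crude finding that patients who walked more were more satisfied or had fewer complications would be printed beside adjusted results and could be taken as support for that idea.

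**Working it through.** **The plan's own figure.** The point disputes no stated figure. The one figure used below is the rule of 5 events per variable (Recruitment and sample size). It reproduces the stated minimum: 5 × 15 = 75 events, and 75 / 0.50 = 150 patients. The 50% share of the rarer outcome class is not stated; it is the value that gives 150.

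**How large could the distortion be?** The documents give no strength of association, so every input here is an assumption. Suppose a baseline factor is present in 35% of patients, lowers walking by *d* SD and lowers the share satisfied. Walking has no effect of its own. Satisfaction is reduced to yes or no.

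Spurious difference in walking (satisfied minus unsatisfied) = *d* × [P(factor | unsatisfied) − P(factor | satisfied)].

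*Satisfied 60% with the factor, 80% without*
- P(satisfied) = 0.35 × 0.60 + 0.65 × 0.80 = 0.73
- P(factor | satisfied) = 0.21 / 0.73 = 0.288
- P(factor | unsatisfied) = 0.14 / 0.27 = 0.519
- Gap = 0.231, so the difference is 0.115 SD at *d* = 0.5 and 0.185 SD at *d* = 0.8

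*Satisfied 55% with the factor, 85% without*
- P(satisfied) = 0.35 × 0.55 + 0.65 × 0.85 = 0.745
- P(factor | satisfied) = 0.1925 / 0.745 = 0.258
- P(factor | unsatisfied) = 0.1575 / 0.255 = 0.618
- Gap = 0.359, so the difference is 0.18 SD at *d* = 0.5 and 0.29 SD at *d* = 0.8

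In 4,000 simulated cohorts of 200 per setting, the unadjusted two-sample test at nominal 5% rejected as follows:

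| Satisfied, with / without factor | *d* = 0.5 | *d* = 0.8 |
|---|---|---|
| 60% / 80% | 10% | 20% |
| 55% / 85% | 18% | 39% |

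**A second set of assumptions.** Here N = 250, the factor is present in 40%, the outcome is binary, and there are 1,000 runs per setting. The odds ratio (OR) for the factor is its effect against a good outcome. Entries are the crude walking OR per SD and the false-positive rate.

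| OR for the factor | *d* = 0.3 | *d* = 0.5 | *d* = 0.8 |
|---|---|---|---|
| 1 | 1.00, 5.3% | 1.00, 4.4% | 1.00, 4.3% |
| 2 | 1.05, 6.9% | 1.09, 7.8% | 1.13, 13.8% |
| 3 | 1.08, 8.3% | 1.14, 19.0% | 1.21, 30.1% |
| 4 | 1.10, 9.6% | 1.17, 20.8% | 1.26, 46.7% |

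With the factor in the model, the walking OR was 1.00 to 1.01 and the false-positive rate about 4% to 6% throughout. That is the best case, because the single factor is fully measured and correctly modelled. No simulation used complications data or the five-point scale.

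**How much adjustment can complications carry?** I apply 5 events to each coefficient, and show the result as a share of the approximately 250 planned patients and of 200 (an assumed analysed number).

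| Model | Coefficients | Events needed | Share of 250 | Share of 200 |
|---|---|---|---|---|
| Walking, age, procedure (2), multi-level, ODQ in five classes (4), depression | 10 | 50 | 20% | 25% |
| Same, ODQ as one continuous term | 7 | 35 | 14% | 17.5% |
| Walking, age, procedure (2) | 4 | 20 | 8% | 10% |

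The documents give no complication rate, so which row is affordable cannot be settled in advance.

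**The case against.** The best defence is one of scope. Satisfaction and six-month complications are not among the four dependent variables, and none of the three research questions mentions them. A crude association is a legitimate descriptive quantity; it misleads only if read causally. The Discussion does not mention satisfaction and does not present complications as something walking would improve. Keeping multivariable models for the named outcomes is a defensible choice, more so where complications may be sparse. This stands, and it is why the point is minor. It does not remove the point, since the Background gives complications a causal expectation and the covariates are already in hand.

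Three stronger readings are tempting, and the documents do not support them.

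- *The associations will be confounded.* Nothing shows that the listed variables affect satisfaction or complications; the confounder list speaks only of outcome in general. Their influence on walking is posed as an open question, and depression, surgical procedure and number of levels are not among the factors to be examined for it. With no link between factor and outcome, the crude analysis is unbiased.
- *The main models are fully adjusted and only these two are not.* The main models keep only variables that pass a bivariate screen, so their adjustment may also be partial.
- *A promised adjustment was dropped.* None was promised for these two outcomes.

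**Conclusion.** The point holds as a modest one. The plan fixes an unadjusted analysis of a non-randomised exposure for two additional outcomes, while collecting variables that it calls confounders and using them, after screening, elsewhere. The two associations are open to confounding.

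Its size cannot be derived from the documents. Under the assumed inputs the false-positive rate runs from near nominal (about 7%) to about 40%, with 47% at the extreme of the second set. The upper values need a factor that lowers walking by 0.8 SD and has a strong effect on the outcome. All of this concerns a simplified binary outcome modelled on satisfaction; for complications the argument is qualitative only. The primary aim and the four main models are not affected.

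**What to change.** Keep the crude results and report an adjusted estimate beside each:

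- **Satisfaction:** an ordinal logistic model for the five-point score.
- **Complications:** a logistic model.
- **Covariates:** walking time plus a small fixed set chosen in advance, namely age, surgical procedure, multi-level surgery, baseline ODQ as a single continuous term, and depression. All are already collected. Pre-operative mobility is scored from one section of the ODQ, so the ODQ term covers it in part.
- **Sparse complications:** reduce the covariates to what the events support at the plan's own 5 per variable (for example age and procedure, 20 events), or use a penalised fit.
- **Labelling:** call both analyses exploratory, so that neither is cited alone in support of promoting walking.

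The cost is two extra models on existing data, and wider intervals for complications if events are few. Adjustment will not remove confounding by factors that are unmeasured or poorly measured.
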